### **9.1.3 Adverse Reaction and Suspected Adverse Reaction**

All noxious and unintended responses to a medicinal product should be considered adverse reactions (AR). Suspected ARs are any AEs for which there is a reasonable possibility that the IMP caused the AE.

AEs associated with the use of the IMP outside what is described in the protocol, including misuse and abuse of the product, are considered as ARs.

### **9.1.4 Unexpected Adverse Drug Reaction**

An “unexpected” AR is an AR, the nature or severity of which is not consistent with the applicable product information (IB EHSG-KF).

### **9.1.5 Suspected Unexpected Serious Adverse Reaction (SUSAR)**

The Sponsor and Investigator evaluate any SAE that has been reported regarding seriousness, causality and expectedness. If the event is at least possibly related to the IMP and it is both serious and unexpected (the nature or severity of which is not consistent with the IB EHSG-KF), it is classified as a SUSAR.

### **9.1.6 Safety Signals**

All suspected new risks and relevant new aspects of known ARs that require safety-related measures.

## **9.2 Recording of Adverse Events and Other Safety Related Events**

Investigators and ultimately the PI have the primary responsibility for AE identification, documentation, and assessment i.e., with regard to seriousness, severity grading, and relatedness to the investigational intervention. This responsibility is applicable during the entire study period, regardless of the relation to the IMP.

Study patients will be instructed to report all AEs and will be routinely questioned about AEs at study visit 2 to visit 12 if possible. The well-being of the patients will be ascertained by neutral questioning (“How are you?”). All AEs will be followed until the event (or its sequelae) resolves or stabilizes at a level acceptable to the Investigators.

All observed or volunteered AEs will be fully documented in the patient file and subsequently recorded in the eCRF. For each AE, the information to be recorded in the source document and in the eCRF includes the nature of the AE, date and time of onset, seriousness, severity, causality (relationship to study product), duration, action taken and outcome of the event.

For all AEs, sufficient information will be pursued and/or obtained so as to permit an adequate determination of the outcome of the event (i.e., whether the event should be classified as a SAE) and an assessment of the causal relationship between the AE and the investigational study treatment. Even if the AE/SAE is assessed by the Investigator as not reasonably related to study product, its occurrence must be recorded in the source documents and in the eCRF. If an AE becomes a SAE, the corresponding eCRF entries are created.

Lack of efficacy per se will not be reported as an AE. The signs and symptoms or clinical sequelae resulting from lack of efficacy will be reported as an AE or SAE if they fulfil the AE or SAE definitions (including clarifications).

All AEs are reported in standardized terminology according to MedDRA adverse event coding dictionary version 18.1. Whenever available, the underlying disease or condition for which a therapeutic or diagnostic procedure is required should be reported as the AE term.

Surgeries or other invasive procedures that had already been planned prior to the enrolment into the study do not have to be documented as SAEs. These planned procedures will be recorded in the eCRF by the Investigator at the baseline visit or as concomitant therapy (whatever applies). It is not important if the condition was known before enrolment, only if the procedure was planned before.

### **9.2.1 Recording of Intermittent Adverse Events**

AEs which occur intermittently during treatment phase and are well known accompanying symptoms also from standard treatment for (large scale) skin defects like:

- Pruritus,
- Pain,
- Granulation tissue,
- Increased temperature/ fever (acute cases),
- Increased heart rate/ tachycardia (acute cases), or
- Nausea (acute cases)

are documented once as “intermittent” with start point (first manifestation) and endpoint (last occurrence of the symptom) in the eCRF. Assessment of causality is done also for all intermittent AEs.

## **9.3 Assessment of Adverse Events and Other Safety Related Events**

The Investigator promptly reviews AEs and abnormal test findings to determine if:

- the abnormal test finding should be classified as an AE (see chapter 9.1.1),
- the AE meets the criteria for a SAE (see chapter 9.1.2), and
- there is a reasonable possibility that the AE was caused by the IMP or study procedures (see chapter 9.3.1).

The severity of an AE will be assessed by the Investigator according to chapter 9.3.2.

### **9.3.1 Relationship Categorization**

The Investigator is required to provide an assessment of relationship of all AEs and SAEs to the study procedure or the IMP. The Investigator should decide whether, in his or her medical judgment there is a reasonable possibility that the event may have been caused by the study procedures or the IMP itself, which includes the following events:

- AEs during the procedure for biopsy harvesting (including events linked to pharmaceutical products that are given to a patient with regard to an upcoming harvesting).
- Suspected microbial transmission from the IMP to the patient.

- AEs with a suspected link to a quality defect of the IMP or ingredient of the IMP (e.g. bovine collagen, media, antibiotics etc.).
- AEs with a suspected link to the application of the IMP (e.g. during grafting).

The assessment of causality to the IMP by the Investigator is done according to the following definitions (Table 9):

**Table 9:** Definition of relatedness

| Relatedness               | Definition                                                                                                                                                                                                                                                                                                                                                                                                                                       |
|---------------------------|--------------------------------------------------------------------------------------------------------------------------------------------------------------------------------------------------------------------------------------------------------------------------------------------------------------------------------------------------------------------------------------------------------------------------------------------------|
| Unrelated                 | 
 
• The event started in no temporal relationship to medicinal product applied and
 
• The event can be definitely explained by underlying diseases or other situations.
 
• An alternate aetiology has been established.
 
• The event does not follow the known pattern of response to study product.
 
• The event does not reappear or worsen with re-challenge.
 
 |
| Unlikely related / remote | 
 
• No temporal association to study product.
 
• Event could readily be produced by clinical state, environmental or other interventions.
 
• The event does not follow the known pattern of response to study product.
 
• The event does not reappear or worsen with re-challenge.
 
                                                                                       |
| Possibly related          | 
 
• Reasonable temporal relationship to study product.
 
• The event is not readily produced by clinical state, environmental, or other interventions.
 
• The event follows a known pattern of response to the study product or as yet unknown pattern of response.
 
                                                                                                               |
| Probably related          | 
 
• There is a reasonable temporal association with the study product.
 
• The event is not readily produced by clinical state, environmental, or other interventions.
 
• The event follows a known pattern of response to the study product.
 
• The event decreases with de-challenge.
 
                                                                                   |
| Definitely related        | 
 
• There is a reasonable temporal association with the study product.
 
• The event is not readily produced by clinical state, environmental, or other interventions.
 
• The event follows a known pattern of response to the study product.
 
• The event decreases with de-challenge and increase with re-challenge
 
                                                     |

If the causal relationship between an AE or SAE and EHSK-KF is determined to be at least possibly related (possibly, probably or definitely related), the event will be considered to be related to EHSK-KF for the purposes of expedited regulatory reporting.

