### **1.1.2 Clinical Summary**

The present proposal is based on the successful completion of the phase I clinical trial in which EHSK-KF was safely grafted as an autologous skin substitute for the reconstruction of burn scars and congenital nevi, and for the coverage of an acute burn, in 10 paediatric patients.

The primary endpoint was safety, as determined by the rates of local infection and graft take. There were no cases of infection, and graft take was acceptable. The mean graft take rate was 63.5% overall (median 78.0%, range 0-100%, SD 36.5%) and 70.6% (range 5-100%, SD 30.6%) when excluding one patient with 100% graft loss attributable to mechanical disruption of the graft post-operatively. Healed skin analogues have been stable thus far without blistering or breakdown.

There were three adverse events deemed to be possibly related to the study product/treatment. There were three severe adverse events (SAE), one that was deemed to be 'unrelated' to the study product/treatment and two that were deemed to be 'possibly related', but importantly all three of these SAEs are also expected complications of conventional grafting surgery. There were no suspected unexpected serious adverse reactions.

In addition, the healed EHSK-KF yielded high quality scars and excellent tissue elasticity, as supported by the POSAS scores. These findings further substantiate the preclinical animal and laboratory studies, supporting EHSK-KF as a viable skin substitute. The clinical phase of the study took place over two years (June 2014-June 2016), and long-term follow-up assessments were carried out annually for five years post grafting concluding in March 2021. For further details please refer to the IB.

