## 9.7 Anticipated Adverse Events

All complications that may be encountered during this study are AEs although they are, in all anticipated likelihood, not a direct consequence of the study product.

Rather, these complications or symptoms are well-known classical findings associated with any type of grafting of skin defects, namely infection, bleeding, unintended mechanical trauma (sheering forces acting upon fresh grafts) that may all lead to partial or complete graft loss. The management of these AEs encompasses additional dressing changes with wound cleansing/wound debridement (including vacuum-system-application), systemic and/or topical antibiotic therapy, and eventually re-grafting operations according to type and severity of the respective complication. In general, these complications are manageable in a straightforward way.

It is more difficult to envision AEs that are truly and solely arising from the use of EHSG-KF given the fact that all viable components are autologous and thus non-immunogenic, and all non-viable components (basically representing extracellular matrix components) have already been used in other clinical contexts without showing any significant AEs.

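### Table 9 has no causality category for an event that follows grafting in time but could also readily be produced by the burn or the surgery, and this conflicts with the reasonable-possibility standard stated around it

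*Protocol*

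**What the plan says.** Protocol section 9.3.1 first asks for the Investigator's medical judgment on whether there is a reasonable possibility that the study procedures or the IMP caused the event. It then says that causality to the IMP is assessed by the definitions in Table 9.

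- *Unrelated* opens with "The event started in no temporal relationship to medicinal product applied and" and goes on to a definite other explanation.
- *Unlikely related / remote* lists "No temporal association to study product" and "Event could readily be produced by clinical state, environmental or other interventions".
- *Possibly related* lists "Reasonable temporal relationship to study product" and "The event is not readily produced by clinical state, environmental, or other interventions", plus a known or as yet unknown pattern of response.
- *Probably related* has the same alternative-cause bullet, a known pattern, and improvement on de-challenge.
- *Definitely related* has the same alternative-cause bullet and "The event decreases with de-challenge and increase with re-challenge".

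The text after the table treats *Possibly* or higher as related for expedited reporting. Section 9.1.5 makes at least possible relatedness one of three SUSAR conditions, with seriousness and unexpectedness. Sections 9.1.3 and 9.3 also use a reasonable-possibility standard. Section 9.7 says of the anticipated complications (infection, bleeding, mechanical trauma, graft loss) that "these complications or symptoms are well-known classical findings associated with any type of grafting of skin defects".

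**The concern.** In most causality scales the middle category is for events where the product is a reasonable suspect and another cause is also credible. In Table 9 that category excludes an event which another cause readily produces, and the two lower categories exclude an event that follows the product in time. The combination left without a row is common in this trial: patients have severe burns, the product is applied surgically, and the complications that the protocol expects are those of any skin graft.

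At stake is consistency between sites, and whether an SAE reaches the line for expedited reporting of an unauthorised cell product. The Italian sub-study (Appendix 2) takes over the same safety section. It enrols patients in a life-threatening situation, has no control area and has death as its primary endpoint, so the clinical state will offer a ready explanation for many serious events there.

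**Working it through.** The protocol gives no figure to reproduce, so the check is logical.

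**Step 1: one typical event.** Take an infection of the EHSG-KF area at the first graft check (day 6–10), readily explained by the burn or by grafting in general.

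| Row | Bullet that decides | Met? |
|---|---|---|
| Unrelated | no temporal relationship | no, the event follows grafting |
| Unlikely | no temporal association | no, same reason |
| Possibly | not readily produced by other causes | no |
| Probably | same bullet | no |
| Definitely | same bullet | no |

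It fits 0 of 5 rows.

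**Step 2: all combinations.** Read each row as requiring all its bullets. Vary temporal relation (yes/no), readily explained otherwise (yes/no), alternative aetiology established (yes/no) and response pattern (known / as yet unknown / none). This gives 2 × 2 × 2 × 3 = 24 profiles. Removing the 2 × 3 = 6 in which an alternative is established but not ready leaves 18. De-challenge and re-challenge are set to not assessable, and the negative re-challenge bullets of the two lowest rows are counted as met.

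- Temporal relation, ready alternative: 6 of 6 fit no row, whatever the response pattern.
- Temporal relation, no ready alternative, known or as yet unknown pattern: 2 of 2 fit *Possibly*.
- Temporal relation, no ready alternative, no pattern: 1 of 1 fits no row.
- No temporal relation: 4 of 9 fit *Unrelated* and/or *Unlikely*; 5 fit no row.
- Total without a row: 6 + 1 + 5 = 12 of 18.

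These are counts of logical combinations. They say nothing about how often each occurs.

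**Step 3: which bullet matters for reporting.** *Possibly* contains no de-challenge or re-challenge bullet, and the 2 profiles that reach it do so with neither assessable. Those bullets put *Probably* and *Definitely* practically out of reach for a graft applied once, but they act only above the reporting line. At the line, the alternative-cause bullet does the excluding.

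**Step 4: the conflict within the section.** Just before Table 9, section 9.3.1 names events to be considered under the reasonable-possibility standard, among them suspected microbial transmission from the IMP and events suspected to be linked to its application. In a burn patient these often have a ready alternative cause. The introductory text would admit them as possibly caused by the product; the *Possibly* row, read literally, would not.

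**The case against.** The strongest counter-argument is that Table 9 never says every bullet must be met; the only joining word is the *and* in the *Unrelated* row. The governing question in section 9.3.1 is medical judgment of a reasonable possibility, and a sensible Investigator will answer that first. An event may also have a plausible alternative cause without being readily produced by it. This stands in part: the gap depends on a conjunctive reading that the table suggests but does not state. That is a reason to state how the bullets combine.

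Safeguards also limit the consequence. All SAEs go to the Sponsor within 24 hours whatever their causality (9.4.1), Sponsor and Investigator both evaluate causality (9.1.5), and an independent board reviews safety (11.5). The AE listings and phase tables in 10.3.8 do not depend on relatedness, and site-level infection is an endpoint of its own. All this stands. It does not close the gap: the initial SAE report must already give the IMP relationship, and the protocol offers no other causality scale.

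Three stronger readings are tempting and not supported.

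- A reader might infer that the de-challenge and re-challenge bullets push SAEs below the reporting line. They cannot, since *Possibly* needs neither.
- A reader might infer that such events automatically become *Unlikely*. They fail that row too; they are unclassified and the assessor has to choose.
- Section 1.1.2 reports two phase I SAEs rated possibly related and adds that "importantly all three of these SAEs are also expected complications of conventional grafting surgery". A reader might conclude that Table 9 would cut related SAEs from two to none. The phase I causality scale is not shown, and being an expected complication of grafting does not establish that another cause readily produced the event in those patients.

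**Conclusion.** The defect holds as a gap and an internal conflict. Read with all bullets required, Table 9 has no row for a temporally associated event with a ready alternative cause (6 of 6 such profiles), and section 9.7 describes the main anticipated complications as being of that kind. The *Possibly* row conflicts with the reasonable-possibility standard in 9.1.3, 9.3 and 9.3.1.

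The consequence is a risk of inconsistent rating, or of rating below *Possibly related*. Systematic under-reporting is not demonstrated and no count of affected events can be given. SUSAR status also needs unexpectedness against the Investigator's Brochure, which is not shown; if infection, bleeding and graft loss are listed there, they would not normally be SUSARs whatever their causality rating. The primary endpoint is untouched. This is a moderate point, worth correcting because the table sets a reporting threshold and the correction is cheap.

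**What to change.** Amend Table 9 as follows.

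1. *Possibly related*: replace the alternative-cause bullet with wording that agrees with a reasonable possibility, for example: the event may also be explained by clinical state, environmental or other interventions.
2. *Unlikely related*: reword so that temporal association alone does not exclude the row, for example: a causal link is improbable and another cause is more plausible.
3. State whether all bullets in a row are required, and how to choose when they conflict.
4. Secondary: remove the de-challenge and re-challenge bullets, or mark them as applying only where assessable. A comparison of the EHSG-KF and control areas should not replace them as a general criterion: the sub-study has no control area, and systemic events cannot be assigned to a site.

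Then re-review causality already recorded under the present wording.

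The cost is an amendment of one table, matching eCRF guidance, and a one-off re-review in a small trial (up to 15 randomised patients planned, plus any sub-study patients, whose number is not stated). The downside is that a few more events may be classed as related and assessed for expedited reporting.

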### 9.3.2 Severity Grading

Severity grading of AEs and SAEs will be assessed using the Common Terminology Criteria for Adverse Events (NCI CTCAE, version 4.03). (Cf. <http://evs.nci.nih.gov/ftp1/CTCAE/About.html>).

In the event that an AE or SAE is not covered by the NCI-CTCAE grading system, the following definitions will be used (Table 10):

**Table 10:** Definition of Grades

| Grade   |                  | Definition                                                                                                                                                                                                    |
|---------|------------------|---------------------------------------------------------------------------------------------------------------------------------------------------------------------------------------------------------------|
| Grade 1 | Mild             | hardly noticeable, negligible impairment of well-being, awareness of sign, symptom, or event, but easily tolerated; does not interfere with usual daily activities or tasks                                   |
| Grade 2 | Moderate         | marked discomfort, but tolerable without immediate relief, discomfort enough to cause interference with usual activity and may warrant therapeutic intervention                                               |
| Grade 3 | Severe           | overwhelming discomfort, calling for immediate relief, incapacitating with inability to perform usual activities and daily tasks; or significantly affects clinical status, requires therapeutic intervention |
| Grade 4 | Life-threatening | immediate risk of death (Note: will require reporting as a SAE)                                                                                                                                               |
| Grade 5 | Death            | Note: will require reporting as a SAE                                                                                                                                                                         |

An AE that is assessed as severe should not be confused with a SAE. Severity is a category used for rating the intensity of an event; both AEs and SAEs can be assessed as severe. An event is described as ‘serious’ when it meets one of the pre-defined seriousness criteria described in chapter 9.1.2.

### 9.3.3 Expectedness

Expectedness of SAEs will be determined by the Sponsor or its representative using the current version of the IB for the IMP.

## 9.4 Reporting of Serious Adverse Events and Other Safety Related Events

### 9.4.1 Reporting of SAEs

The Investigator is responsible for reporting any SAEs to the Sponsor immediately within 24 hours of the Investigator’s first knowledge of the event, even if the event does not appear to be related to the IMP or the study procedures. Submission is done by entering and saving the SAE in the eCRF, which sends an automatic email to the Sponsor.

Initial SAE report: the initial SAE report must be as complete as possible, including details of the current illness and SAE, and an assessment of the causal relationship between the event and the IMP or study procedures.

The following information is a minimum set of information required for all initial SAE reports:

- Investigator name
- Patient identifiers
- AE term(s)
- Suspected IMP
- IMP relationship
- Reason why the event is serious

Follow-up SAE report: Information not available at the time of the initial report (e.g., an end date for the SAE, laboratory values received after the report, or hospital discharge summary) must be documented as a follow-up in the eCRF. Additional follow-up information, if required, or available, should be recorded in the eCRF and must be reported by the site every 14 days until resolution or stabilization of the SAE.

At any time after completion of the AE reporting period, if an Investigator becomes aware of a SAE that is suspected by the Investigator to be related to the IMP or study procedures, the event must be reported to the Sponsor or its representative.

In case reporting via eCRF is not working, a filled out SAE report form can be sent via:

- email to [[contact]](mailto:[contact]),
- fax to [contact] (back up procedure for email submission), or
- post to Julius Clinical, Safety Group, [name], [name], The Netherlands.

In case of SAE submission by fax or e-mail, the originals of the SAE report forms (both initial and follow-up report) will be collected by the monitor. The sites keep a copy for their own records.

